## Abstract

**Background:**

Chemotherapy-induced peripheral neuropathy (CIPN) is a progressive, enduring, and sometimes irreversible neurotoxic symptom that occurs in 30–40% of chemotherapy-treated cancer patients. CIPN negatively affects both the patient’s abilities to perform daily activities and their health-related quality of life (HRQOL) after chemotherapy treatment. Although this neuropathy has been treated with duloxetine and/or gabapentin, limited therapeutic benefits have been reported, thereby necessitating the development of an integrated approach that combines pharmacological management and complementary methods such as acupuncture and electric nerve stimulation. Therefore, this study is designed to examine the effect of a portable, low-frequency electrostimulation (ES) device on CIPN symptoms and HRQOL of female patients diagnosed with CIPN immediately after chemotherapy for breast cancer.

**Methods:**

This study is a single-center, randomized, placebo-controlled trial with two parallel groups and a 2-week follow-up. We will enroll 80 breast cancer patients who are newly diagnosed with CIPN after chemotherapy. Duloxetine or pregabalin will be prescribed to all participants from the initial assessment. Half of the patients will be assigned into the experimental group and the other half to the control group. The CarebandR (Piomed Inc., Seoul, Korea), a wearable wristband that generates low-frequency electrostimulation, will be administered only to the experimental group. Electrostimulation will be administered on the unilateral PC6 acupoint. A numerical rating scale will be used to assess the overall intensity of CIPN symptoms. The key secondary outcome variables include patient-reported CIPN symptom distress tested by a self-rated questionnaire, physician-rated symptom severity assessed by the Total Neuropathy Score, and HRQOL.

**Discussion:**

It is expected that the combination of a low-frequency electrostimulation device and pharmacological intervention (duloxetine or pregabalin) will produce synergistic effects in breast cancer patients with CIPN after treatment. To our knowledge, this is the first study to investigate the beneficial effect of a new integrated approach for CIPN management after breast cancer treatment. The study findings can expand our knowledge and understanding of the occurrence of CIPN and the efficacy of integrated intervention efforts to ameliorate CIPN symptoms.

**Trial registration:**

Clinical Research Information Service (CRIS), Republic of Korea, ID: KCT0002357. Registered retrospectively on 13 June 2017*.*

**Electronic supplementary material:**

The online version of this article (10.1186/s13063-018-2874-2) contains supplementary material, which is available to authorized users.

## Background

According to the latest national cancer statistics, the prevalence rate of breast cancer in Korea has increased more than three times in the past 10 years and the 5-year cancer survival rates have increased from 77.9% in 1993–1998 to 91.5% in 2008–2013 [1, 2]. It is noteworthy that the number of premenopausal breast cancer patients in Korea is significantly higher than those in Western countries, which can be attributed to the fact that the highest prevalence rate is found in women aged 40 to 49 years [3]. Women diagnosed with breast cancer at age 50 years or younger reported to have poorer health-related quality of life (HRQOL) than their older counterparts because they may face various HRQOL issues for the entire trajectory of their cancer diagnosis and treatment [4]. HRQOL has been perceived as an important clinical outcome for long-term survivorship among women living longer with cancer. For this reason, the balance between survival advantages from curative therapy and HRQOL challenges has received special attention from healthcare professionals as well as breast cancer patients.

Anticancer treatment, especially chemotherapy, was associated with acute or late toxicities which affected post-treatment HRQOL after treatment [5, 6].

Chemotherapy-induced peripheral neuropathy (CIPN) is a commonly reported symptom affecting HRQOL in chemotherapy-treated breast cancer patients [7, 8]. This is referred to as any damage, inflammation, or degeneration of the peripheral nerves because of the administration of certain chemotherapeutic agents such as paclitaxel, docetaxel, or vincristine [9]. CIPN manifests as sensory, motor, and autonomic symptoms. Sensory neuropathy is the most common but motor symptoms and autonomic dysfunctions may occur [10]. Symptoms of sensory neuropathy include numbness, tingling, burning of hand and feet, loss of sensation, paresthesiae, and occasionally pain. Motor symptoms present as impaired motor nerves, weakness of muscles, and muscle atrophy. Symptoms associated with autonomic nervous system dysfunction include constipation, orthostatic hypotension, and urinary incontinence [11]. The neuropathy symptoms affect the patient’s quality of life and can cause long-lasting complications [11].

Clinically, CIPN has been treated with duloxetine and/or gabapentin. Duloxetine is a serotonin and norepinephrine dual reuptake inhibitor that can reduce pain due to the suppression of painful peripheral stimuli transmission [7]. Gabapentin can inhibit neuronal activity and thus produces analgesic effects through the reduction of excitatory neurotransmitter release [12]. The American Society of Clinical Oncology guidelines suggest that these agents are useful in managing CIPN during and after chemotherapy [13]. However, many studies have demonstrated mixed results on the efficacy of pharmacological interventions on CIPN in individuals treated with chemotherapy for various types of cancer such as breast and colorectal cancer. Interestingly, one phase 3 randomized crossover trial reported that there was no significant change in CIPN symptoms between patients treated with 2700 mg of gabapentin for CIPN and disease- and treatment-matched controls who received placebo treatment [14]. Moore et al. reported that about 74% of patients who have painful neuropathic pain can expect neuropathic pain control [15]. Due to the limited therapeutic benefits of medication for CIPN treatment, a number of studies suggest that complementary methods can be used for the treatment of CIPN in cancer patients and survivors [16, 17]. These studies have shown that various types of acupuncture, including manual acupuncture, electroacupuncture, and auricular acupuncture, have positive effects on pain symptoms in patients with cancer [16, 18]. In other studies, acupuncture-like transcutaneous electric nerve stimulation (TENS) also produced similar effects on sensory and motor symptoms of CIPN through a possible mechanism of top-down pain regulation of the central nervous system [19, 20]. Previous experimental studies have demonstrated that the analgesic effects of electroacupuncture on neuropathic pain were produced by antinociception, which involves μ, δ, or κ opioid receptors, spinal serotonin, and norepinephrine, and changes in the concentrations of excitatory and inhibitory amino acid neurotransmitters to stop the pain. The actions of electroacupuncture were also associated with glial cells and cytokines and other bioactive molecules [21]. Park et al. [22] reported that CIPN-induced pain was reduced by using electroacupuncture in patients who were treated with eight cycles of chemotherapy, including docetaxel and taxane agents. Smith et al. reported that an electrocutaneous nerve stimulation device (MC5-A Calmare) reduces CIPN pain by 20% [20]. Taken together, pharmacological treatment yields clinically beneficial effects on CIPN management, but the combination of other supportive interventions with current conventional treatments is required to complement the limited efficacy of using medication alone. Moreover, the aforementioned supportive interventions require patients to be in a fixed position for a certain period of time. To ensure that patients comply with the treatment for CIPN, the development of interventions that allow patients to work while receiving treatment anywhere and anytime is crucial.

Therefore, the purpose of this study is to examine the effect of a portable, low-frequency electrostimulation device on CIPN symptoms and HRQOL of female patients diagnosed with CIPN immediately after chemotherapy for breast cancer.

## Methods/design

This study is a single-center, randomized, placebo-controlled trial with two groups and a 2-week follow-up. The treatment period was determined based on previous studies [20, 22–27]. The trial will be conducted at the Chungnam National University Hospital Cancer Center from March 2017 to December 2018. Trained researchers will enroll 80 breast cancer patients who are newly diagnosed with chemotherapy-induced peripheral neuropathy. Patients who meet the eligibility criteria will be recruited and randomly allocated into intervention or control groups in a 1:1 ratio. The overall flow of the trial is shown in Fig. 1. The protocol of this study has been reviewed and approved by the Institutional Review Board of Human Research of the Chungnam National University Hospital (2016–11-020). Informed consent will be obtained from all individual participants before starting any data collection in this study. The protocol fulfills the populated Standard Protocol Items: Recommendations for Interventional Trials (SPIRIT) Check list and Figure (as Fig. 2) and the SPIRIT Checklist is attached as Additional file 1.

**Fig. 1 Fig1:**
[figure not shown]
Flow chart of the trial

**Fig. 2 Fig2:**
[figure not shown]
Measures

### Participants

Participants will be considered for enrollment if they meet the eligibility criteria and have a score of at least 5 on a numeral rating scale(NRS) used to assess overall intensity of CIPN symptoms after completion of chemotherapy for primary breast cancer [28]. Inclusion criteria will be determined by one oncologist and one neurologist. Also, severe CIPN will be determined by the neurologist. More detailed eligibility information on the eligibility criteria is presented in Table 1.

**Table 1 Tab1:** Patient eligibility criteria

Inclusion criteria	Exclusion criteria
Female, at least 19 years old	Patients with a history of receiving chemotherapy for cancer before this diagnosis was made
Patients diagnosed with primary breast cancer	Patients with symptoms of peripheral neuropathy that are severe and need to be immediately treated with surgical procedures or acute management
Patients with a diagnosis of CIPN presenting within the first week of an average pain score of at least 5 on a visual analogue scale of pain after completion of chemotherapy	Patients with pre-existing peripheral neuropathy due to trauma or intercurrent illness
Patients who do not take any medication to prevent or treat neuropathy before screening	Patients with skin inflammation at the attachment site
Patients with an ECOG performance status of 2 or less	Patients with a history of previous use of an acupressure wristband over a week. Patients with a history of cardiovascular disorders including the use of a pacemaker
Patients who are willing and able to comply with the requirements of the study	Patients with known hypersensitivity to metal or any medication
Patients who are willing and able to provide written informed consent	Patients with uncontrolled hypertension (systolic blood pressure ≥ 170 mmHg or diastolic blood pressure ≥ 100 mmHg) or uncontrolled diabetes
	Patients with hepatic insufficiency or dysfunction (three times higher than normal levels of ALT, AST, creatinine)
	Patients who were pregnant or are potentially pregnant and breastfeeding
	Patients with psychiatric disorders or who take medication for psychiatric illnesses
	Patients with a history of receiving investigative, new drugs within 4 weeks before enrollment
	Patients who do not have the ability to read, understand, or respond to questionnaires
	Patients with other reasons not to comply with this study protocol

*CIPN* chemotherapy-induced peripheral neuropathy, *ECOG* Eastern Cooperative Oncology Group, *AST* aspartate transaminase, *ALT* alanine aminotransferase

### Sample size

Sample size will be decided by the primary outcome. According to the published study on low-frequency electroacupuncture treatment for CIPN, the overall change in mean scores between baseline and 2-week follow-up was − 4.0 with a significant decrease in pain over time [27, 29]. However, there was no previous study that could provide data to compute standardized differences between two means of two groups in calculating the sample size for this trial. Accordingly, this study will evaluate the efficacy and feasibility of the low-frequency wristband intervention for patients with CIPN [30]. With consideration for the maximum number of subjects needed in pilot studies and the central limit theorem, a total sample size of 40 per group was calculated [31]. The sample size was calculated based on the changes in the NRS between baseline (visit 2) and the end of the study (visit 3). Based on two previous studies [26, 29], the mean and standard deviation are conservatively assumed. We calculated that 32 patients per group would be required to achieve a power of 95% with a two-sided significance level of *p < 0.05* for detecting the superiority of treatment with Careband R by a *t* test. Here, the assumed effect size (*d*) was 2.33. To account for possible dropouts (10%), the target number of patients was, therefore, set at 40 per group (80 in total) (see below):$$ {\displaystyle \begin{array}{l}\mathrm{n}=2\kern1em {\left\{\frac{\left({\mathrm{Z}}_{1-\upalpha /2}+{\mathrm{Z}}_{1-\upbeta}\right)\kern0.5em \ast \kern0.5em \upsigma}{\varDelta}\right\}}^2\\ {}\mathrm{n}=2\kern1em {\left\{\frac{\left(1.96+1.64\right)\kern0.5em \ast \kern0.5em 2.57}{2.33}\right\}}^2\\ {}\mathrm{n}=31.63\end{array}} $$

*H*_*0*_: *d*_*t*_ *= d*_*c;*_
*H*_*1*_: *d*_*t*_ *≠ d*_*c*_*;* d_*t*_: the changes in the NRS between baseline (visit 2) and the end of the study (visit 3) of the intervention group; *d*_*c*_: the changes in the NRS between baseline (visit 2) and the end of the study (visit 3) of the control group; *Δ*; *d*_*t*_ − *d*_*c*_.

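### Ten per cent dropout on 32 per group gives 36, not the stated 40, and the 2.33 labelled as effect size d is a raw difference in NRS points

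*Protocol article*

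**What the plan says.** All the statements are in the Sample size section of the protocol article.

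- **Target size, first account.** After noting that "there was no previous study that could provide data to compute standardized differences between two means of two groups", the section turns to the maximum size for pilot studies and the central limit theorem, and says that on this basis "a total sample size of 40 per group was calculated".
- **Base calculation.** It then gives a power calculation on the change in NRS from visit 2 to visit 3. For this, "the mean and standard deviation are conservatively assumed" from two cited studies, and "32 patients per group would be required to achieve a power of 95" per cent, with "a two-sided significance level of" 0.05 and a t test. The displayed formula uses σ = 2.57 and Δ = 2.33 and ends at 31.63.
- **Effect label.** The text adds: "Here, the assumed effect size (*d*) was 2.33". Below the formula, Δ is defined as the intervention group's NRS change minus the control group's.
- **Target size, second account.** "To account for possible dropouts (10%), the target number of patients was, therefore, set at 40 per group (80 in total").

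**The concern.** The sentence on dropout presents 40 as the consequence of two stated numbers, 32 and 10%, and they do not produce it. A reader who checks the step cannot tell whether the dropout rate, the base figure or the target is wrong. The earlier pilot-study account of the same 40 adds to the doubt, because the section does not say which reasoning set the size.

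The label on 2.33 is a separate slip. In the usual notation, d is a standardised difference. Anyone who lifts the sentence without the formula would report an assumed effect about 2.6 times too large (2.33 against 0.91). The section also uses d with subscripts for raw NRS changes, which adds to the confusion.

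At stake is whether the stated justification of the trial's size can be followed and reused, and what dropout allowance was really made. Protection against a false negative at the stated difference is not at risk.

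**Working it through.** **Inputs, all from the Sample size section:** two-sided α = 0.05 (z = 1.96); power 95% (z printed as 1.64); σ = 2.57; Δ = 2.33 NRS points; dropout 10%; target 40 per group. The 1:1 allocation is in the Randomization section.

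**1. The plan's base figure.** n = 2 × {(z₁₋α/₂ + z₁₋β) × σ / Δ}².

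- With the printed values: 2 × {(1.96 + 1.64) × 2.57 / 2.33}² = 2 × (3.971)² = 31.53.
- With 1.645 for the second value: 2 × {3.605 × 2.57 / 2.33}² = 31.62.
- Both round up to 32. The printed 31.63 differs only by rounding, so the base figure reproduces.

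This formula is a normal approximation. The section names a t test, for which power from the noncentral t distribution is 94.6% at 32 per group and 95.2% at 33. The gap of one patient is trivial.

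**2. The dropout step.**

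| Base n per group | n / 0.90 | n × 1.10 | Rounded up | Dropout implied by 40 |
|---|---|---|---|---|
| 32 | 35.6 | 35.2 | 36 | 1 − 32/40 = 20% |
| 33 | 36.7 | 36.3 | 37 | 1 − 33/40 = 17.5% |

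Neither inflation rule, from either base, gives 40. From the plan's own 32, the result is 36 per group, or 72 in total: 4 per group and 8 overall below the stated target.

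**3. What the discrepancy does to power.** If 40 per group are enrolled and 10% are lost, 40 × 0.90 = 36 remain. Exact t-test power at Δ = 2.33 and SD 2.57:

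| Evaluable per group | Power |
|---|---|
| 32 | 94.6% |
| 33 | 95.2% |
| 36 | 96.7% |
| 40 | 98.0% |

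**4. The label.** The formula divides σ by 2.33, and Δ is defined as a difference between two NRS changes, so 2.33 is in NRS points. The standardised effect is 2.33 / 2.57 = 0.91. If 2.33 were really standardised (σ = 1), the normal formula would give 2 × (3.605 / 2.33)² = 4.8, so 5 per group, and the exact t test would need 6 (95.2% power). The 32 therefore rests on the raw reading. The formula is right and the label is wrong.

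**5. The source of 2.33 and 2.57.** The section says that no earlier study supplies a standardised two-group difference, and then takes a mean and SD from two earlier studies. It does not show how 2.33 or 2.57 follows from them. The only outcome figure quoted from earlier work is an overall change of −4.0 from baseline to 2 weeks, which does not enter the formula. Whether the values are conservative cannot be checked from the document.

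**The case against.** The strongest reply is that nothing is harmed. The target exceeds what the inputs require, power at the stated difference is above 95%, and the pilot-study rationale may be the true origin of 40, with the power calculation serving only to show that 40 is enough. The formula prints 2.57 beside 2.33, so a careful reader can see that 2.33 is not standardised. All of this stands as regards consequence. It does not rescue the text: the dropout sentence says that 40 follows from 10% attrition, and the label is wrong as printed.

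Three stronger readings are tempting, and the document does not support them.

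- **That calling the assumption conservative contradicts the admitted lack of two-group data.** It does not. Choosing a cautious value because direct data are missing is coherent, and 2.33 is well below the quoted change of 4.0 (2.33 / 4.0 = 58%). What can be said is that the derivation is not shown.
- **That 2.33 is a before-and-after change borrowed from a different treatment.** The Discussion does describe a group of references that includes 26 and 27 as scrambler therapy. But the mean and SD are credited to 26 and 29, and that description does not cover 29. Nothing says that 2.33 is a within-patient change, and Δ is defined as a between-group contrast.
- **That the power claim makes a null result uninterpretable.** Power is lower at smaller differences in any trial. The document states no smaller important difference against which to judge this one, and the Data analysis section plans analysis of covariance, so t-test power at other values need not be that of the planned analysis.

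**Conclusion.** The point holds as an error in the stated derivation and in a label. Ten per cent dropout on 32 per group requires 36 (72 in total), not 40 (80 in total). Forty corresponds to 20% dropout, or to the separate pilot-study argument, and the section must say which. The 2.33 is a raw between-group difference in NRS change, with a standardised value of 0.91. The provenance of 2.33 and 2.57 is undocumented, which is a lesser weakness.

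A reader might infer from a faulty sample-size paragraph that the trial is too small. On its own inputs it is not: the base figure of 32 is correct, and the error runs in the safe direction, with about 96.7% power at 36 evaluable per group. That figure assumes a true difference of 2.33 points, SD 2.57, 10% loss in each group, no contribution from patients lost, and an unadjusted two-sample t test. The correction is worth making because it is cheap and readers rely on the paragraph, but the design does not need to change.

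**What to change.** Keep 80 patients and rewrite the paragraph as a single line of reasoning:

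1. State that 32 evaluable patients per group are needed by the normal formula (94.6% power by the exact t test; 33 for 95%).
2. State that 10% dropout on 32 requires 36 per group.
3. State that 40 per group was retained on the pilot-study rationale, if the sponsor confirms that this is where it came from, leaving 36 evaluable and about 96.7% power at 2.33 points. Replacing 10% with 20% merely to make the arithmetic close would be a rate chosen to fit, and should be avoided unless 20% was the real planning assumption.
4. Replace the effect-size label with a raw between-group difference of 2.33 NRS points, SD 2.57, standardised effect 0.91.
5. Show how 2.33 and 2.57 were obtained from the two cited studies, or remove the word claiming that they are conservative.

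The cost is wording only. Enrolment, analysis and conduct are unaffected, so the correction can be made while recruitment continues.

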### Randomization

A total of 80 participants who meet the eligibility criteria will be randomly assigned in a ratio of 1:1 to the intervention or the placebo control group. The concomitant use of neuropathy medications during the study is a confounding factor that can influence the outcomes of the study. For this reason, the randomization will be stratified according to the use of medication administered for neuropathy. A randomization code list was generated using SAS version V9.4 (SAS Institute Inc., Cary, NC, USA) by a statistician who is not involved in this study. The randomization procedure will be conducted by a research assistant who will not take part in the interview, data collection, intervention, or statistical analysis. Obtaining informed consent and baseline data will be completed before randomization. A link between the randomization code and the corresponding treatment will remain blinded for all other members in the study team.

### Recruitment strategies

Potential candidates will be invited by a physician in the study team and will be given the details of this clinical trial. A secondary recruiting strategy, such as advertisements in the cancer center, will also be applied at the same time. Participants who meet the eligibility criteria and are willing to participate will be enrolled after they read and sign an informed consent form.

### Intervention

At baseline, the interventional medical devices and placebo medical devices will distributed to the participants allocated in the electrostimulation (ES) group and the placebo control group, respectively. The device that is used to manage CIPN symptoms is CarebandR (Piomed Inc., Seoul, Korea), which is a wearable wristband that generates low-frequency electrostimulation. The placebo wristband device, which does not generate an electrical stimulus and has an identical appearance, will be administered to the placebo control group. Both interventional and placebo devices are labeled identically for blinding of participants. The participants will be educated to use the devices on the second stage (100 μA, 40 Hz) or above for 14 days, at least twice a day, for at least 120 min, which includes one consecutive hour of use. Electrostimulation will be administered on the unilateral PC6 acupoint, which is located approximately three finger breadths above the wrist crease between the palmaris longus tendon and flexor carpi radialis tendon [32]. The PC6 acupoint was selected for its applicable location and therapeutic effects of regulating *qi*, tranquilizing, and relieving pain.

